## Intervention

The ‘Care for Stroke’ intervention will be delivered through a smartphone and it will include information about stroke and the ways to manage poststroke disabilities. The intervention includes 2–3 min of 60 videos in vernacular language organised in five sections. The sections are: (1) information about stroke, (2) home-based exercises, (3) functional skills training, (4) activities of daily living, and (5) assistive devices. The intervention will be self-directed, with participants seeking information in the different categories as they require. The intervention will also have an option for the stroke survivor or the identified caregiver to contact the intervention provider for any technical support in accessing the intervention through smartphone.

## Intervention arm

The stroke survivor and their caregiver will receive 45–60 min of training on accessing and use of the intervention (watching videos) via the smartphone. Participants will then be provided with a smartphone preloaded with the ‘Care for Stroke’ intervention and asked to try it out on their own. Three or more errorless attempts to retrieve any required part of the intervention from the smartphone will be considered successful training. After successful training, participants will be provided with a smartphone loaded with the intervention and will be asked to use this intervention at their discretion at home over a 6-week period.

The identified caregivers of stroke survivors will be asked to support the stroke survivors as and when necessary to access the intervention from the smartphone. The participants will be telephonically supported at least once in a week during the intervention period. The telephonic support is essentially to remind and obtain updates from the participants or identified caregivers on utilisation of the intervention. A summary of this conversation will be documented and the notes will be kept privately in a locked cupboard. The participants in the intervention arm will not be restricted from receiving standard treatment for their stroke.

## Control arm

Participants in the control arm will receive standard poststroke rehabilitation services. In general, the standard treatment may include provision of physiotherapy (45 to 60 min) at home or in a clinic facility for the stroke survivors based on goals set by the specific therapist or a rehabilitation team.

## Outcome measures

### Primary outcome

The primary outcome measure is dependency in activities of daily living and will be measured by the MRS^27^ at baseline and at 6 weeks after randomisation. The MRS scale measures the degree of disability or dependence in the activities of daily living of people who have suffered a stroke in six categories. The scores range from 0 (no symptoms) to a maximum of 6 (dead). A dichotomous approach to outcome analysis will be used. Participants’ scores will be categorised into MRS scores of 0–3 and 4–6.

## Secondary outcome

Secondary outcome measures will be:Modified Barthel Index.^24^Modified Caregiver Strain Index.^28^Quality of Life measured by World Health Organization - Quality of Life Brief (WHOQOL–BREF).^29^Use of healthcare and rehabilitation services (therapy, hospitalisation and medication, AYUSH, traditional practices and so on).This information will be collected through questionnaire at baseline and after 6 weeks. The smartphone application has an inbuilt monitoring mechanism where the usage of the intervention by the participants will be tracked.

Costs for rehabilitative care will be collected from participants both in the treatment groups to see whether the Care for Stroke intervention delivered through a smartphone reduces the overall costs of care (cost-effectiveness).Direct costs of healthcare and rehabilitation since the time of stroke.Indirect costs (a family member giving up paid employment and taking the role of a caregiver, travel costs and so on).

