**Methods:**

The objective of the study is to evaluate whether the ‘Care for Stroke’ intervention is clinically and cost-effective for the reduction of dependency in activities of daily living among stroke survivors in an Indian setting. This study is designed as a randomised controlled trial comparing people who received the intervention to those receiving standard care. The trial will be pragmatic and outcome assessor-blinded. The primary outcome for the study is dependency in daily living measured by the Modified Rankin Scale (MRS). A total of 266 adult stroke survivors who fulfil the eligibility criteria will be randomised to receive either ‘Care for Stroke’ intervention or standard treatment and will be followed up for 6 weeks. The main analyses will compare participants allocated to the ‘Care for Stroke’ intervention versus those allocated to the standard treatment group on an ‘intention-to-treat’ basis, irrespective of whether the participants received the treatment allocated or not. The dichotomised MRS scores (0–3 and 4–6) in both the groups will be used to calculate the effect estimates with a measure of precision (95% CI) and presented in the results of the trial.

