## Setting

### Participant recruitment

Participants will be identified using their contact details from treatment records for their first ever stroke. These details for stroke survivors in India exist in two places. Participant diagnosis and details can be collected from the hospital records from which an individual received treatment for his/her stroke. It is also available at the government health insurance department where the cost of the treatment for stroke is covered by this insurance department. Hence, participants will be identified through both these options. The identified participants will be contacted at their home for consent and recruitment. The intervention will be provided to the participants at home and they will be asked to use the intervention in their home.

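### Direct costs are counted from the stroke and not from randomisation, and lower cost is labelled cost-effectiveness with no delivery cost listed

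*Protocol article*

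**What the plan says.** The abstract (Methods) sets out to evaluate whether the intervention is "clinically and cost-effective for the reduction of dependency in activities of daily living among stroke survivors in an Indian setting". The Introduction adds that cost-effectiveness will inform planning and scale-up.

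The cost outcome is described under Secondary outcome:

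- Source: "Costs for rehabilitative care will be collected from participants both in the treatment groups".
- Purpose: "to see whether the Care for Stroke intervention delivered through a smartphone reduces the overall costs of care (cost-effectiveness", with that last word standing in parentheses as the name for reduced cost.
- Direct component: "Direct costs of healthcare and rehabilitation since the time of stroke".
- Indirect component: "Indirect costs (a family member giving up paid employment and taking the role of a caregiver, travel costs and so on". No time window is given for it.

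On timing, Participant recruitment states: "Participants will be identified using their contact details from treatment records for their first ever stroke". Randomisation describes a telephone contact, a home visit, consent and a baseline form before allocation. The inclusion criteria require only a recent stroke, with no limit in days. Follow-up says that all outcomes, primary and secondary, are evaluated at baseline and at 6 weeks.

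On delivery, Intervention arm gives 45–60 minutes of training and telephone support at least weekly for 6 weeks, and says: "After successful training, participants will be provided with a smartphone loaded with the intervention". The Intervention section adds technical support on request.

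**The concern.** Three features of the cost outcome sit badly with the question it is meant to answer.

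1. The direct-cost window opens at the stroke. Everything between stroke and randomisation is fixed before allocation and carries no treatment effect. The length of that period is not limited and can differ between people. Including it adds variation and no information.
2. The article equates lower cost with cost-effectiveness. An intervention can cost more and be cost-effective, or cost less and not be, so a test of cost reduction does not answer the abstract's objective.
3. The listed costs are those collected from participants. The smartphone, training and calls are supplied by the trial, and a participant questionnaire would not normally capture them. If nothing else is added, the intervention arm is compared without its own price.

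At stake is the cost-effectiveness conclusion that the abstract promises and that the Introduction ties to decisions on implementation.

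**Working it through.** The documents give no cost, cost SD or stroke-to-randomisation interval, so there is no stated figure to reproduce. The check is a reading of the sections together, plus an illustration under stated assumptions.

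**Step 1: does the window precede randomisation?** Direct costs start at the stroke (Secondary outcome). Participants are identified from records of treatment already given (Participant recruitment) and allocated after a home visit (Randomisation). So the window as defined includes pre-randomisation spending. No section says that this part is subtracted or adjusted for.

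**Step 2: what does that do to the comparison?** Write a participant's total as T = A + B, with A the cost from stroke to randomisation and B the cost from randomisation to 6 weeks. Randomisation makes the expected A equal in both arms, so the expected difference in T equals the expected difference in B: no bias. For precision, let SD(A) = k × SD(B) and let ρ be their correlation:

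Var(T) = Var(B) × (1 + k² + 2ρk)

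With ρ = 0, the standard error of the arm difference is multiplied by f = √(1 + k²). The equivalent share of the sample is 1/(1 + k²). A comparison with 80% power on B (two-sided 5%) has power Φ((1.960 + 0.842)/f − 1.960) on T.

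| k (assumed) | 1 + k² | SE multiplier f | Equivalent sample | Power, from 80% |
|---|---|---|---|---|
| 0.5 | 1.25 | 1.12 | 80% | about 71% |
| 1 | 2 | 1.41 | 50% | about 51% |
| 2 | 5 | 2.24 | 20% | about 24% |

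Positive correlation raises the multiplier: at k = 1 and ρ = 0.5 it is √(1 + 1 + 1) = 1.73. If the baseline figure A is subtracted, T − A = B and the multiplier returns to 1.

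**Step 3: delivery cost.** Per participant in the intervention arm, D = smartphone + one training session (45–60 minutes) + at least 6 calls (one a week × 6 weeks). No unit prices are given, so D cannot be valued. If D is not counted, the reported incremental cost is too low by exactly D per participant. Unlike the noise in step 2, this does not shrink with sample size, and randomisation does not remove it.

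**Step 4: the label.** The abstract ties cost-effectiveness to reduced dependency, which needs cost and effect together. Secondary outcome uses the term for reduced cost alone. The two do not match.

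**The case against.** The strongest reply is that this is a short data-collection list in a condensed article. The Analysis section describes no cost analysis, so the window may describe what is asked and not what is compared. Because all outcomes are assessed at baseline and at 6 weeks, the post-randomisation cost may be obtainable by subtraction. Costing of the device, training and calls would come from the trial's own accounts, so its absence from a list of participant-reported costs is unsurprising; an economic analysis plan may supply it. The formal Objective and the Overview do not mention cost-effectiveness.

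Much of this stands, and it rules out several stronger readings that a reader might infer:

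- *That pre-randomisation spending biases the result.* It does not; it balances in expectation.
- *That the comparison would be overwhelmed by noise.* That needs a large k, and no cost SD is given. At k = 0.5 the loss is modest.
- *That delivery costs are excluded.* The article does not say that participant-reported costs are the only ones counted. It lists no delivery cost, which is less.
- *That the acute hospital bill is necessarily in the total.* Participant recruitment says that the insurance department covers the cost of stroke treatment for those in its records, so participant-reported costs may hold little of it.

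What the reply does not remove is the wording that is present. The window is defined as cumulative from the stroke, and cost reduction is given the name of cost-effectiveness. Both are stated, not left to another document. The planned baseline assessment makes the correction easy, but it does not make the definition right.

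**Conclusion.** The point holds in a limited form. As defined, the direct-cost outcome includes spending before randomisation that the intervention cannot change. The consequence is lost precision: a standard error 1.12, 1.41 or 2.24 times as large for k = 0.5, 1 or 2, assuming independent earlier costs that are neither subtracted nor adjusted for. The values of k are illustrative.

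The article also uses the term cost-effectiveness for a test of cost reduction, which does not answer the abstract's objective. It lists no delivery cost; whether one will be counted elsewhere cannot be told from the article. If none is counted, the comparison favours the intervention by the full per-participant delivery cost.

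This concerns a secondary outcome that carries a headline claim. The MRS result does not depend on it.

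**What to change.** - Define the cost comparison as costs from randomisation to 6 weeks in both arms, collected at the baseline and 6-week assessments already planned.
- Use costs from stroke to randomisation only as a baseline covariate.
- Add the delivery cost (smartphone, training, calls) to the intervention arm from the trial's own accounts, or point to the document that already does so.
- Report the incremental cost alongside the difference in the proportion with MRS 0–3, with a confidence interval. Otherwise, call the analysis a cost comparison and drop the term cost-effective from the abstract and Secondary outcome.

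The cost is a small change to the questionnaire's recall window, an extract from the trial accounts and a few lines of text. The incremental cost will look less favourable to the intervention than a figure without delivery costs.

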## Follow-up

An outcome form will be completed at 6 weeks after randomisation or at death, if either happens sooner. A blinded outcome assessor will evaluate all the outcomes (primary and secondary) at baseline and at 6 weeks. A relatively short follow-up period has been selected as The Stroke Therapy Academic Industry Round Table strongly recommends a shorter follow-up period to reduce variation in clinical outcome that could occur due to subsequent stroke events that are unrelated to the trial.^24^ This will also allow accurate assessment of the outcome.^30^

## Adverse events

Adverse events are very common among acute stroke survivors. Some of the expected adverse events during the trial are as follow:Death due to any vascular causes (eg, myocardial infarction, recurrent stroke).Hospitalisation due to poststroke complications such as infections, brain oedema, seizures, deep vein thrombosis, urinary tract infections, pressure sores and shoulder subluxation, dislocation and fracture.Occurrence of secondary stroke.

These events will be documented during follow-up telephone calls and it will be presented to an independent data safety and monitoring committee for unblinded review.

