## Randomisation

Stroke survivors will receive all-usual treatment for stroke. Participants eligible for inclusion will be identified by a trial investigator. The eligible participants will be initially contacted by telephone and they will be visited in person at their home by the investigator to share the details about the study to the participant and the identified caregiver. A participant information sheet outlining the study objectives, risks and benefits along with brief information sheet about stroke will be provided to the participant. Written informed consent for participation in the intervention will be sought from all participants or from the next of kin if the participant is unable to consent.

An entry form will be used to collect baseline information including the contact details of the participant and the identified caregiver. This information will be forwarded to the independent randomisation centre and the participants eligible for inclusion will be randomised to the intervention or control arm in a 1:1 ratio using a secure, central, password-protected, web-based system. The intervention will be started within 24 hours of randomisation.

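### Adverse events are to be recorded in follow-up telephone calls, but the only calls described after randomisation belong to the intervention arm, so ascertainment could differ by arm

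*Protocol article*

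**What the plan says.** The *Adverse events* section of the protocol article gives examples of expected events: vascular death, hospital admission for complications after stroke, and secondary stroke. It then fixes how they are recorded, "These events will be documented during follow-up telephone calls", and where they go: they are "presented to an independent data safety and monitoring committee for unblinded review". It does not say which arm is called, who calls, or how often.

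Calls after randomisation are described in one place only, *Intervention arm*: "The participants will be telephonically supported at least once in a week during the intervention period". Their purpose is also stated there: "The telephonic support is essentially to remind and obtain updates from the participants or identified caregivers on utilisation of the intervention". The *Control arm* section says "Participants in the control arm will receive standard poststroke rehabilitation services" and mentions no calls.

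The follow-up common to both arms is a single assessment: "An outcome form will be completed at 6 weeks after randomisation or at death, if either happens sooner". Under *Secondary outcome*, a questionnaire at baseline and six weeks asks about healthcare use, including hospitalisation. Neither form is named as a source of adverse events.

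**The concern.** An event is counted only if somebody asks about it or hears of it. If one arm is telephoned every week and the other is not, the first arm has more chances for an event to be recorded, even when the true risk is the same. The caller in the intervention arm also cannot be blind to allocation, because the call is about use of the intervention.

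Two uses of the data are exposed. The monitoring committee reviews the events unblinded, so it can see counts by arm. It could read a difference in recording as a difference in harm, or not hear of some events among controls. Any safety table published by arm would carry the same distortion.

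**Working it through.** The plan states no adverse event rate, capture rate or expected count, so there is no figure of its own to reproduce. The check has two parts: a comparison of the sections, and an illustration of size.

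**Contacts after randomisation, as described**

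- *Intervention arm*: at least one call a week for six weeks, so at least about 6 × 1 = 6 calls per participant.
- *Intervention*: the participant or caregiver may "contact the intervention provider for any technical support in accessing the intervention through smartphone". This contact is started by the user and exists only for those who have the intervention.
- *Control arm*: no calls described, so 0.
- *Randomisation*: "The eligible participants will be initially contacted by telephone". This is a recruitment call made before consent and randomisation, so it is not follow-up.
- *Follow-up* and *Secondary outcome*: one outcome form at six weeks or at death, and one six-week questionnaire, in both arms.

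By the named route, then, the text describes at least about six recording opportunities per intervention participant and none per control.

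**Which events are exposed**

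- Death: recorded in both arms on the outcome form, and it is also the top score of the primary outcome scale.
- Hospitalisation: asked about in both arms in the six-week questionnaire.
- Secondary stroke without death or admission: no common route described.
- Other complications that do not lead to admission: no common route described. The section presents its list as examples, so such events are not ruled out.

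**Size**

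Let r be the true six-week risk, equal in both arms, and let cI and cC be the proportions of events captured in the intervention and control arms. The recorded risks are r × cI and r × cC, so the spurious ratio is cI / cC and r cancels. All capture rates below are assumptions.

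- 90% v 85%: 0.90 / 0.85 = 1.06
- 95% v 80%: 0.95 / 0.80 = 1.19
- 90% v 50%: 0.90 / 0.50 = 1.80
- 95% v 50%: 0.95 / 0.50 = 1.90

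To show the scale in counts, take the planned 133 per arm and an assumed risk of 10%. With 95% capture the intervention arm records 133 × 0.10 × 0.95 = 12.6 events. The control arm records 133 × 0.10 × 0.80 = 10.6 at 80% capture, or 133 × 0.10 × 0.50 = 6.7 at 50%. Changing the risk to 5% or 20% changes the counts but not the ratios.

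The common route reduces this. If a share s of events is captured at 90% in both arms through the six-week forms, and the rest at 90% v 50%, the overall ratio is 0.90 / (0.90 − 0.40 × (1 − s)). It runs from 1.80 at s = 0 to 1.00 at s = 1. This dilution applies only if the adverse event tabulation actually draws on those forms, which the article does not say.

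**The case against.** The strongest reply is that the two kinds of call should not be merged. The *Adverse events* section does not say that its calls are the weekly support calls, and the support calls are given a different purpose. The section covers the whole trial, and unblinded review by a committee fits collection in both arms. A call schedule for each arm may stand in the full protocol. This has force: a reader might infer that adverse events will be collected only from the intervention arm, and the document does not establish that. It supports *could*, not *would*. It does not dispose of the point. The article does not leave ascertainment open; it names telephone calls as the route and describes such calls for one arm only.

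A second reply is that the listed events are serious, that a co-resident caregiver is required, and that death and hospitalisation are already collected in both arms. Infections and fractures appear in the list only as causes of admission. This stands, and it narrows the point to non-fatal events that do not lead to admission.

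Third, no formal comparison of adverse events between arms is planned: *Objective* has no safety aim, and *Analysis* specifies effect estimates only for the dichotomised primary outcome. This also stands. What is exposed is the committee's review and any safety comparison that is later reported.

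Fourth, the larger ratios come entirely from the capture rates chosen. That is right, and none of them should be read as a prediction.

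**Conclusion.** The point holds in a limited form. As the article is written, the named route for adverse events is asymmetric: calls are described for the intervention arm and not for controls. Non-fatal events captured nowhere else could therefore be over-represented in the intervention arm, and the caller there would know the allocation.

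The size is unknown. With equal true risk the spurious ratio is the ratio of capture rates: about 1.06 if capture is 90% v 85%, up to 1.8 if it is 90% v 50%. The lower end is more plausible for deaths and admissions, which have a common six-week route.

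A reader might go further and infer that the trial's main result is biased. The document does not support that, because the primary outcome is rated at six weeks in both arms by a blinded assessor. The conclusion rests on the calls described in the article being the only ones. If the full protocol schedules identical calls in both arms, what remains is a clarification of the text.

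**What to change.** Reconcile *Adverse events*, *Intervention arm* and *Control arm*, so that it is clear which calls are meant, who receives them, who makes them and how often.

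Base every by-arm tabulation of adverse events, including the one given to the monitoring committee, on one source used identically in both arms. A structured checklist on the existing six-week outcome form, completed by the blinded assessor, would do this. It should cover death, hospitalisation and its cause, secondary stroke, and the other listed complications.

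Events heard in support calls should still go to the committee, as a separate listing labelled as collected in one arm only and not for comparison. No safety information is then lost, although the committee will still hear of some intervention-arm events sooner.

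The cost is a few items on a form that is already planned, and some recall loss over six weeks, which should be similar in both arms. The sample size and the primary analysis do not change.
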